## Abstract

**Background:**

Inferior scapular notching is a complication unique to reverse shoulder arthroplasty. The most efficient technique to avoid inferior scapular notching has been reported to be lateralization of the glenoid offset. This study aims to compare radiological and functional outcomes of the DELTA Xtend® Reverse Shoulder System Lateralized Glenosphere Line Extension (intervention group) with the Standard DELTA Xtend® Reverse Shoulder System (control group). We hypothesize that the lateralization improves the patient outcome by decreasing the risk of inferior scapular notching without increasing the risk of migration and loosening of glenoid component.

**Methods:**

In this randomized controlled trial, all Danish citizens with rotator cuff arthropathy or degeneration of the glenohumeral joint with severe posterior wear and allocated for a reverse total shoulder arthroplasty at the department of orthopaedic surgery at Herlev and Gentofte Hospital, Copenhagen University Hospital, will be considered for participation. The exclusion criteria are as follows: below 50 years of age, cognitive or linguistic impairment, insufficient glenoid bone stock, previous fracture in the upper extremity and autoimmune-mediated inflammatory arthritis. There will be included a total of 122 patients of which 56 will participate in the radiostereometric analysis. This number of patients allows 20% to drop out. The co-primary outcomes are the pattern and magnitude of the migration of the glenoid component assessed by radiostereometric analysis and the Western Ontario Osteoarthritis of the Shoulder index. The secondary outcomes are inferior scapular notching, patient-reported and functional outcomes (Oxford shoulder score, Constant-Murley score and pain), side effects and complications, changes in bone mineral density and economy. The included patients will be examined before the surgery, within 1 week and 3, 6, 12 and 24 months after.

**Discussion:**

No previous studies have compared the conventional reverse shoulder arthroplasty with the lateralized reverse shoulder arthroplasty in a randomized controlled trial regarding migration and functional outcome. Furthermore, radiostereometric analysis has not been used to evaluate the migration of reverse shoulder arthroplasty in a randomized controlled trial. This study intends to determine which treatment has the most optimal outcome for the benefit of future patients with an indication for reverse shoulder arthroplasty.

**Trial registration:**

The study has been notified to Pactius and has approval number P-2021-231. Furthermore, the study will be registered on Clinicaltrials.gov before starting the inclusion.

**Supplementary Information:**

The online version contains supplementary material available at 10.1186/s13063-022-06482-8.

## Background

Reverse total shoulder arthroplasty is the preferred implant for patients with degeneration of the glenohumeral joint and wear or tear of at least one rotator cuff tendon [1, 2], and the aim of the surgery is pain relief, improved range of motion and relatively low risk of revision surgery [3, 4].

Inferior scapular notching, which is damage to the inferior part of the bone of the glenoid component, is a complication unique to reverse shoulder arthroplasty and was described and graded by Sirveaux et al. in 2004 [4] and reported that 63% of the patients showed signs of inferior scapular notching. A more recent study [5] reported inferior scapular notching in 10% of 476 reverse shoulder arthroplasty implants and found lower clinical outcome scores, lower strength and range of motion (ROM) when present. Both studies found higher revision rates in this subgroup of patients [4, 5]. Furthermore, Roche et al. [6] reported that inferior scapular notching may decrease glenoid baseplate stability which might ultimately lead to aseptic loosening in the clinical situation.

Different techniques to avoid inferior scapular notching have been reported [7]. Lawrence et al [8] reported that the most efficient technique was to use a lateral offset of the glenoid component. Previous studies have found that a lateralized design of the reverse shoulder arthroplasty led to improved rotation and a lower risk of scapular notching [9, 10].

Theoretically, the lateralized design can be associated with a greater risk of loosening of the glenoid component due to the tilt forces [9, 10]. Migration and loosening of the glenoid component can have severe consequences, not only for the patients but also for healthcare providers. Thus, even few extra revisions can make the lateralized component less attractive from an economic point of view.

Plain x-rays are unable to detect minor implant migration and authors have recommended that radiostereometric analysis should be used instead [11, 12]. By inserting small tantalum beads into the surrounding bone, implant migration can be measured extremely accurate [13]. Technical advances within radiostereometric analysis have made it possible to identify the implant and its position using the geometry of the implant instead of attaching tantalum beads to the implant (model-based radiostereometric analysis).

In shoulder arthroplasty surgery, radiostereometric analysis has been used to study the migration of the glenoid component in anatomical total shoulder arthroplasty [14, 15] and, in a few cases, migration of hydroxy-coated resurfacing humeral components [16, 17]. Previous studies have used radiostereometric analysis to access migration of the reverse shoulder arthroplasty [18, 19]. To our knowledge, conventional reverse shoulder arthroplasty and lateralized reverse shoulder arthroplasty systems have not been compared in a randomized design regarding the clinical outcome and patient-reported outcome.

This randomized controlled trial aims to compare the DELTA Xtend® Reverse Shoulder Lateralized Glenosphere Line Extension System (intervention group) to the Standard Delta Xtend® Reverse Shoulder System (control group) (Depuy Synthes, Raynham, MA, USA). We hypothesize that the lateralization improves the patient outcome by decreasing the risk of inferior scapular notching without increasing the risk of migration and loosening of glenoid component.

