### Outcome measures

#### Primary radiological outcome

Migration of the glenoid components is assessed by model-based radiostereometric analysis, which is performed according to the guidelines of Valstar and Colleagues [12]. In this part of the study, the first 56 patients are included. Maximum total point motion (MTPM) after 2 years of follow-up is compared to the baseline value and is used as the primary radiostereometric analysis effect parameter. The accuracy of radiostereometric analysis will be assessed by at least 12 double examinations. The reference examination will be done within 1 week after the surgery, and the follow-up examinations are planned at 3 months, 6 months, 1 year and 2 years. Radiostereometric analysis is conducted using a uniplanar radiostereometric analysis arrangement (UmRSA®- Calibration Cage No 43 (hip, spine and shoulder)). The x-ray analysis is performed using the model-based radiostereometric analysis commercial software (RSAcore, Department of Orthopedics, Leiden University Medical Center, Leiden, The Netherlands), available at the Skaane University Hospital, Lund Sweden, where the analyses of radiostereometric analysis-x-rays will be conducted. The exact set-up for the radiostereometric analysis (e.g. various distances and the degree between the 2 x-ray tubes) will be specified from a small phantom study and measurements of the 6 pilot patients (3 with each of the 2 types of implants). 42 combined CAD models for MB-RSA will be delivered by Depuy Synthes (Raynham, MA, USA).

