### Statistics

Prior to the analysis, the nature of the data is assessed. It is expected to analyse the changes between pre- and postoperative assessment with paired parametric statistics. The differences between the groups are expected to be analysed using parametric statistics (Student *t*-test). The radiostereometric analysis data is not expected to be normally distributed and will be analysed using non-parametric analysis of variance over time. The differences between these groups will be analysed with Mann-Whitney *U* test. Because of the nature of repeated measures in this study, it is expected to use a mixed effects model to analyse the overall results. Data on radiostereometric analysis and DXA will be analysed at the end of follow-up for the first 56 patients. No other interim data-analysis will be carried out.

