### Sample size calculation radiostereometric analysis

Sample size calculation for radiostereometric analysis (maximum total point motion of the glenoid component after 2 years will be used as primary radiostereometric analysis effect parameter) was performed with an expected standard deviation (SD) of 0.4 mm, a minimally clinically important difference of 0.4 mm, a significance level at 5% and power of 0.90 and resulted in 22 participants in each group (56 participants with allowance for 20% drop-out) [26]. There are no data metrics for migration of the glenoid component in reverse shoulder arthroplasty, but the sample size fits with estimates in previous studies comparing two different orthopaedic implants. The argument is that RSA has high accuracy and, therefore, that few patients are needed [12].

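### The migration hypothesis is a non-inferiority claim, but the migration co-primary is sized and tested as a difference, with no margin, so a non-significant result could be misread as showing no increase

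*Protocol article*

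**What the plan says.** The Background section, like the Abstract, hypothesizes benefit by "decreasing the risk of inferior scapular notching without increasing the risk of migration and loosening of glenoid component". The Abstract gives migration primary status: "The co-primary outcomes are the pattern and magnitude of the migration of the glenoid component assessed by radiostereometric analysis", alongside the WOOS index. The section on the primary radiological outcome names the parameter: "Maximum total point motion (MTPM) after 2 years of follow-up is compared to the baseline value".

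The radiostereometric (RSA) sample size uses an "expected standard deviation (SD) of 0.4 mm" and "a minimally clinically important difference of 0.4 mm, a significance level at 5% and power of 0.90". This gives 22 per group, or 56 patients after a 20% drop-out allowance. The same section says that no migration data exist for the glenoid component of a reverse arthroplasty.

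The Statistics section expects RSA data not to be normal. It plans a non-parametric analysis of variance over time and then says: "The differences between these groups will be analysed with Mann-Whitney" (the U test). A mixed effects model is expected for the overall results. No non-inferiority or equivalence margin, one-sided bound or interval criterion for migration is stated anywhere in the article.

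**The concern.** A claim that something is not increased needs evidence that rules out an increase of a size that matters. A test of difference asks whether equality can be rejected. If it is not rejected, a relevant excess may still be compatible with the data. The hypothesis and the planned test therefore answer different questions.

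The direction of the error matters. Fewer usable RSA images or noisier measurements make a non-significant result more likely, so poorer data would appear to support the hypothesis more easily. The protocol has its own reasons to care about a modest excess. The Background expects that tilt forces could raise the risk of loosening and notes that even a few additional revisions would count against the device. The Discussion foresees adoption without further testing if an advantage is found.

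This is not a detail that a condensed article leaves to the statistical analysis plan. The article states the hypothesis, the sizing and the test, and they do not match.

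**Working it through.** **Inputs.** From the RSA sample-size section: SD 0.4 mm, difference 0.4 mm, significance level 5%, power 0.90, 22 per group, 56 in all with 20% drop-out. Allocation is 1:1 (Study design). Sidedness is not stated; two-sided is inferred because it reproduces the stated n.

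**1. The protocol's own figure.**
n per group = 2 × (1.96 + 1.2816)² × (0.4/0.4)² = 21.01, rounded up to 22. Power of the t-test at 22 per group is 0.8997. Drop-out: 22/0.8 = 27.5, rounded up to 28 per group, 56 in all. The figure reproduces as a two-sided test of difference.

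**2. What a non-significant result leaves open (22 evaluable per arm).**
SE = 0.4 × √(2/22) = 0.1206 mm. The critical t on 42 df is 2.018, so an observed excess up to 2.018 × 0.1206 = 0.243 mm is non-significant. Its upper 95% limit can reach 0.243 + 0.243 = 0.487 mm (0.4868 before rounding), above the protocol's own 0.4 mm. With 28 per arm, SE = 0.1069 mm, the critical t on 54 df is 2.005 and the half-width is 0.214 mm.

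**3. Chance of a non-significant result when migration is truly greater.** Noncentral t, normal data, SD 0.4 mm:

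| True excess | 22 per arm | 28 per arm |
|---|---|---|
| 0.2 mm | 63% | 55% |
| 0.3 mm | 32% | 21% |
| 0.4 mm | 10% | 4% |

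Simulated Mann-Whitney tests on normal data (20,000 runs, 22 per arm) give 64%, 34% and 12%. At a true excess of 0.2 mm, about 28% of trials with 22 per arm (14% with 28) are non-significant while the upper 95% limit still reaches 0.4 mm or more.

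**4. Sensitivity to non-normality.** The protocol gives no mean MTPM. Assuming lognormal data with control SD 0.4 mm and control mean 0.4 to 0.8 mm, Mann-Whitney at 22 per arm is non-significant in about 21% to 68% of trials at +0.2 mm, and in under 1% to about 26% at +0.4 mm. The result depends on the mean and on whether the excess is a shift or proportional, so the table can be wrong in either direction.

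**5. Sensitivity to poorer data.** For a true excess of 0.4 mm and normal data, 18 evaluable per arm (assumed) gives 17% non-significant, and SD 0.6 mm with 22 per arm (assumed) gives 42%. A rule that compares the upper limit of the two-sided 95% interval with 0.4 mm holds that error at about 2.5% in both cases.

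**6. Power of a non-inferiority rule.** Upper limit of the two-sided 95% interval below the margin, no true difference, normal data, SD 0.4 mm:

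| Margin (assumed) | Power, 22 per arm | Power, 28 per arm | n per arm for 0.90 (normal approximation) |
|---|---|---|---|
| 0.4 mm | 0.90 | 0.96 | 22 |
| 0.3 mm | 0.68 | 0.79 | 38 |
| 0.2 mm | 0.37 | 0.45 | 85 |

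**The case against.** - **Intended reading.** A reader might infer that the investigators plan to treat a non-significant Mann-Whitney test as proof of safety. No section says so. The Statistics section says only that differences will be analysed, so the supportable statement is that the result could be misread.
- **Other migration evidence.** The plan is not limited to one p-value. It includes an analysis over time and a mixed effects model, which can give an estimate with an interval. Revisions are recorded, and the Discussion points to continuing migration after the first year as a sign of later loosening. All this stands, but none of it supplies a criterion for saying that migration is not increased.
- **Difference framing is coherent elsewhere.** The stated aim is to compare the implants, and detecting a 0.4 mm excess with 0.90 power is a reasonable way to look for harm. That supports keeping the test. It does not let a failure to detect harm confirm the hypothesis.
- **Use of the result.** The written condition for adoption in the Discussion mentions infection, not migration. Migration should therefore not be called the condition on which adoption rests, although it is a co-primary outcome and part of the hypothesis.
- **Normality.** The main figures use a model that the protocol does not expect to hold. This is correct, and it is why they are approximate.
- **Unseen analysis plan.** It could contain an interval rule. It would then have to change the inferential basis that the protocol states.

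**Conclusion.** The point holds as a mismatch: the migration part of the hypothesis is a non-inferiority claim, and the stated sizing and test address a difference without a margin. The stated analysis cannot confirm that part of the hypothesis. The size is a 63% to 55% chance of a non-significant result at a true excess of 0.2 mm, and 10% to 4% at 0.4 mm, for 22 to 28 evaluable per arm. This rests on normal data, SD 0.4 mm and a two-sided 5% test.

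A reader might also infer that the RSA part is underpowered. The documents do not support that: with a 0.4 mm margin and no true difference, the planned number suffices. Nor can one infer that 0.4 mm is an acceptable margin. The protocol presents it as "a minimally clinically important difference of 0.4 mm" and has no migration data for this implant type, so the sponsor must justify whichever margin is chosen.

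**What to change.** Keep the Mann-Whitney comparison and add a decision rule in the hypothesis, statistics and sample-size text:

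1. Conclude that migration is not increased only if the upper limit of the two-sided 95% interval for the between-arm difference in 2-year MTPM lies below a pre-stated, justified margin. The Hodges-Lehmann interval matches the planned test; use a bootstrap interval if a pure shift is implausible.
2. Fix and justify the margin before any RSA results are compared, with the protocol's own 0.4 mm as the largest candidate.
3. State that a non-significant test alone does not support the claim.
4. Restate the power for the chosen margin. At 0.4 mm and no true difference, 22 per arm (56 in all) gives about 0.90 and the size stands. For a smaller margin, keep the size and report the lower power: about 0.68 at 0.3 mm and 0.37 at 0.2 mm with 22 per arm.

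The cost is wording only, with no extra patients or examinations. The downside is that a wide interval must be reported as inconclusive, which becomes more likely as the margin gets smaller.

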## Methods and design

### Study design

This study is an investigator initiated, single-centre, 1:1 randomized controlled trial, which will compare the DELTA Xtend® Reverse Shoulder Lateralized Glenosphere Line Extension (intervention group) with the standard DELTA Xtend® Reverse Shoulder System (control group). The two implants are produced by Depuy Synthes (Raynham, MA, USA). The SPIRIT reporting guidelines [20] and checklist (Additional file 1: Appendix 1) were used.

### Method

Inclusion criteria:Rotator cuff arthropathy defined as degeneration of the glenohumeral joint and wear or tear of at least one rotator cuff tendonDegeneration of the glenohumeral joint with intact rotator cuff function but severe posterior wear of the glenoid (> 20° posterior wear)Insufficient effect of non-surgical treatment with symptoms severe enough to justify shoulder arthroplasty.ASA (American Society of Anesthesiology) score 1–3, physically fit for surgery and rehabilitation

Exclusion criteria:Below 50 years of ageCognitive or linguistic impairmentInsufficient glenoid bone-stockPrevious fracture in the upper extremitiesPatients with autoimmune-mediated inflammatory arthritisGlenoid border medial to the medial border of the coracoid on a true AP radiograph (Fig. 1)

**Fig. 1 Fig1:**
[figure not shown]
Assessment of medialization on true AP radiograph

### Enrolment

All Danish citizens with the diagnosis of rotator cuff arthropathy (degeneration of the glenohumeral joint and wear or tear of at least one rotator cuff tendon) or degeneration of the glenohumeral joint with severe posterior wear with an indication of a reverse total shoulder arthroplasty referred to the orthopaedic department at Herlev and Gentofte Hospital, Copenhagen University Hospital, will be considered for participation in the trial. Elective surgery is only performed on patients with a Danish civil registration number, which is given at birth or immigration. Thus, no foreign citizens will be included in the trial. The medical records will be reviewed by the treating surgeon, who will evaluate if the patient can participate in the study, based on the above-mentioned inclusion and exclusion criteria. The patients will not be included in the study if the glenoid surface is medial to the medial border of the coracoid process on a true AP x-ray. The measurement is done by the following steps on true AP x-ray: (1) the coracoid process is identified; (2) a reference line is drawn horizontal on the acromion; (3) a perpendicular line is drawn to the acromion reference line, passing through the lateral side of the coracoid process base; (4) a perpendicular line is drawn to the acromion reference line passing through the medial side of the coracoid process base; and (5) the glenoid base is identified (Fig. 1). If the criteria are fulfilled, the treating surgeon will pass information (Additional files 2 and 3: Appendices 2 and 3) to the primary investigator (Fig. 2), and participation will be offered to the patient. The patients who are interested in participation are invited for an undisturbed consultation with the treating surgeon. If the surgeon determines the patient to be eligible, the patient will receive written and oral information about the project. Additionally, the patient will be informed of the possibility to bring a witness for the last consultation before surgery, which is the time point where the surgery is planned and where the patient gives informed consent. This consultation held with the primary investigator, is minimum 24 h later than the previous consultation, minimum 24 h prior to the surgery and in an undisturbed room. The patient and a possible witness will be re-informed of the study and the informed consent (Additional file 4: Appendix 4) will be collected if the patient accepts to participate. Thereby the patient has had minimum 24 h to reflect on the decision and the opportunity to bring a witness.

**Fig. 2 Fig2:**
[figure not shown]
CONSORT flow diagram of the progress of the study

The patients will then be asked to complete four questionnaires (Oxford Shoulder Score (OSS), Western Ontario Osteoarthritis of the Shoulder index (WOOS score), EQ- 5D-5 L and pain with the visual analogue scale (VAS-score)). The informed consent gives the primary investigator access to information regarding medication, occupation, age, gender, comorbidity and education, from medical records and questionnaires. Furthermore, the patients will have an examination with measurement of the activity of daily living, pain, strength (Constant-Murley score), range of movement and a radiographic examination with plain radiographs with standard anterior-posterior and lateral projections, MRI of the index shoulder joint and CT scan. The glenoid medialization will be measured by using true AP radiograph (Fig. 1). Dual-energy x-ray absorptiometry (DXA) is used to assess bone mineral density (BMD) and osteopenia of the proximal humerus and distal forearm.

The patients will get an extra radiation dosage of 0.10 mSV including all the tests, which corresponds to the background radiation of 12 days in Denmark. In addition to the standard treatment the participating patients will have additional radiographic examinations including radiostereometric analysis, plain radiographs and DXA (Figs. 3 and 4).

**Fig. 3 Fig3:**
[figure not shown]
SPIRIT figure. Schedule of enrolment and assessments of the 56 radiostereometric analysis patients

**Fig. 4 Fig4:**
[figure not shown]
SPIRIT figure. Schedule of enrolment and assessments of the 66 patients who are not included in the radiostereometric analysis study

